## Abstract

**Background:**

Mental health disorders in the context of long-term conditions in children and young people are currently overlooked and undertreated. Evidence-based psychological treatments for common childhood mental health disorders (anxiety, depression and disruptive behaviour disorders) have not been systematically evaluated in young people with epilepsy despite their high prevalence in this population. The aim of this multi-site randomised controlled trial is to determine the clinical and cost-effectiveness of adding a modular psychological intervention to usual care for the mental health disorders in comparison to assessment-enhanced usual care alone.

**Methods:**

In total, 334 participants aged 3–18 years attending epilepsy services will be screened for mental health disorders with the Strengths and Difficulties Questionnaire (SDQ) and the diagnostic Development and Wellbeing Assessment (DAWBA). Those identified as having a mental health disorder and consenting to the trial will be randomised to either receive up to 22 sessions of the modular psychological intervention (MATCH-ADTC) delivered over the telephone over 6 months by non-mental health professionals in addition to usual care or to assessment-enhanced usual care alone. Outcomes will be measured at baseline, 6 months and 12 months post-randomisation. It is hypothesised that MATCH-ADTC plus usual care will be superior to assessment-enhanced usual care in improving emotional and behavioural symptoms. The primary outcome is the SDQ reported by parents at 6 months. Secondary outcomes include parent-reported mental health measures such as the Revised Children’s Anxiety and Depression Scale, quality of life measures such as the Paediatric Quality of Life Inventory and physical health measures such as the Hague Seizure Severity Scale. Outcome assessors will be blinded to group assignment. Qualitative process evaluations and a health economic evaluation will also be completed.

**Discussion:**

This trial aims to determine whether a systematic and integrated approach to the identification and treatment of mental health disorders in children and young people with epilepsy is clinically and cost-effective. The findings will contribute to policies and practice with regard to addressing mental health needs in children and young people with other long-term conditions.

**Trial registration:**

ISRCTN ISRCTN57823197. Registered on 25 February 2019.

## Background and rationale {6a}

Children and young people with epilepsy who also have mental ill-health are poorly served by current health care provision. The mental health disorders often go undetected and undiagnosed, treatment when provided is often inadequate and service organisation fails to integrate and co-locate physical and mental health care [1]. This is despite the evidence that co-occurring mental ill-health impacts on physical health and quality of life and, in adults, increases chance of death [2, 3].

The protocol described here is for a randomised controlled trial (RCT) designed to address aspects of this problem. The clinical trial forms Work Package 3 of a broader research programme aimed at developing a new psychological treatment for anxiety, depression and behavioural problems in children with epilepsy.

The background and rationale for the research programme as a whole is embedded within a wider national priority within the UK National Health Service (NHS) - namely the closer integration of mental and physical health care [4]. Epilepsy is the most common serious neurological disorder in childhood, affecting approximately 1 in 150 children [5]. Evidence-based psychological treatments for common childhood mental health disorders (anxiety, depression and disruptive behaviour disorders) have not been systematically evaluated in young people with epilepsy despite their high prevalence in this population [6–9]. Although epilepsy is defined by recurrent seizures, the comorbid mental health disorders such as anxiety and depression often have a greater impact on quality of life [10]. One reason for the failure to apply psychological treatments may be current service organisation. Such patients are seen in paediatric services and, if mental health input is needed, are referred to local Child and Adolescent Mental Health Services (CAMHS). However, CAMHS are overstretched [11] and inexperienced in dealing with mental ill-health in the context of a long-term condition [12].

The Modular Approach to Therapy for Children with Anxiety, Depression, Trauma or Conduct problems (MATCH-ADTC) is a psychological intervention which is compliant with UK recommended best practice with modules that are selected to treat multiple common mental health disorders in youth [13–15]. It draws from psychological theories to encourage positive behaviours and reduce unhelpful ones and is based on principles of cognitive behaviour therapy (CBT) for managing behaviour problems, anxiety, depression and trauma in children. The treatment contains therapeutic procedures that were selected to correspond to the practices found in several leading evidence-based psychological treatments (EBTs), against which MATCH was compared in randomised trials [14, 15]. Despite extensive trial literature demonstrating the efficacy of evidence-based psychological treatments [16], they are disappointingly rarely implemented in clinical practice [17]. The MATCH-ADTC protocol and manual modular design ensures that the needs of individuals with multiple mental disorders (40% of patients) are met - in contrast to the protocol for the majority of trials which address only single, specific disorders [18].

MATCH-ADTC is divided into 33 practice modules that correspond to four focus areas with corresponding coordinating modules. The first focus area/coordinating module is for anxiety disorders and the practice modules within this correspond to the strategies in ‘Coping Cat’ [19]. The second focus area is for the treatment of depression and the modules within this corresponds to the strategies in ‘Primary and Secondary Control Enhancement Training’ (PASCET) [20]. The third focus area is for Parent Training for behavioural problems [21]. The fourth focus area is for trauma. Both Coping Cat and PASCET have been used successfully in children with physical illnesses and comorbid mental health conditions [22]. According to the protocol, the therapist focuses on the initial problem area identified by the patient and family together with the information gathered in the clinical and research assessment. It is considered to represent true evidence-based practice in that the protocol combines research evidence, clinical judgement and patient values and preferences [23]. Once a problem area has been selected (e.g. anxiety), an algorithm specifies a default sequence of focus area and practice modules and guides clinical judgement. However, the intervention is also personalised so that if the default sequence cannot be implemented (e.g. due to low mood), then the sequence can be changed to address the immediate issue. Once the interfering issue has been addressed, treatment for the original problem area is resumed. Carers and family members can join the telephone/video conferencing sessions where appropriate and in the original trial 41% of the sessions included the child plus a family member [14].

Focus groups with patients and family members identified the need for an epilepsy-specific focus area/coordinating module, which was not a component of the published MATCH-ADTC protocol. This was felt necessary to meet the needs of young people with both epilepsy and mental health disorders. Epilepsy-relevant content was integrated throughout the treatment, such as epilepsy-related examples in worksheets. The epilepsy materials were developed and finalised in earlier stages of the programme of research [24].

### Objectives {7}

The overarching aim of this programme of research is to transform the treatment of mental health disorders in young people with epilepsy by systematically identifying and treating mental health problems from within epilepsy services to enable early detection and intervention.

Specifically, the trial aims to determine the clinical and cost-effectiveness of adding a personalised modular psychological intervention—MATCH-ADTC with epilepsy-relevant content integrated throughout and an additional epilepsy-specific focus area, with one compulsory and three optional modules—to assessment-enhanced usual care. Assessment-enhanced usual care is usual care with the addition of standardised assessment measures, since those in this arm will have completed the Development and Well-being Assessment (DAWBA) and the results of the DAWBA will be provided to clinicians and to participants. The intervention will be delivered by non-mental health specialists, over the telephone/online, within epilepsy services, for young people with epilepsy who also meet Diagnostic and Statistical Manual of Mental Disorders (DSM-5) diagnostic criteria for a mental health disorder.

### Trial design {8}

This study is a two-arm randomised controlled superiority trial comparing the clinical and cost-effectiveness of MATCH-ADTC in addition to usual care for mental health disorders in epilepsy to assessment-enhanced usual care alone.

Patients aged 3–18 years within epilepsy services (and their accompanying parent/carer) will be approached. The process of determining eligibility will involve being asked some brief questions, completing the Strengths and Difficulties Questionnaire (SDQ) [25, 26] and, if above the threshold, providing informed consent before completing a full computerised psychiatric diagnostic assessment (the Development and Wellbeing Assessment: DAWBA [27]). Those meeting diagnostic criteria for a mental health disorder according to this assessment will be invited to take part in the trial. Participants will be individually randomised to usual care only or to usual care plus the MATCH-ADTC intervention. The primary outcome measure is the total difficulties score from the SDQ reported by the parent/carer at 6 months post-randomisation. The primary analysis will be conducted on an intention-to treat basis and blind to treatment assignment. All measures will be repeated 1 year post-randomisation to examine whether any improvements in mental health are maintained as a secondary outcome.

## Methods: participants, interventions and outcomes

### Study setting {9}

Recruitment will be from any epilepsy clinic setting, ranging from highly specialist to general hospitals, and from a range of populations served. All sites are in the UK. Therapists will be NHS staff working within epilepsy services and will include epilepsy nurse specialists, pre-qualification psychology assistants, neurologists, neuropsychologists and support workers. A full list of participating sites is available from http://www.isrctn.com/ISRCTN57823197.

### Eligibility criteria {10}

Participants will be considered eligible for enrolment in this trial if they fulfil all the inclusion criteria and none of the exclusion criteria as defined below.

#### Participant inclusion criteria

Attending NHS epilepsy clinics.Aged 3–18 years.Scoring above the pre-specified threshold on the SDQ for mental health symptoms which is a combination of raised total difficulty score (≥ 14) and raised impact score (≥ 2).Meeting DSM-5 diagnostic criteria for a mental health disorder (e.g. depression, anxiety, disruptive behaviour or trauma) identified by the SDQ, the Development and Wellbeing Assessment (DAWBA) and clinical assessment.Have a parent/carer who is also willing to take part in the study.

#### Participant exclusion criteria

Not speaking/understanding English sufficiently well to access the screening assessments.Having an intellectual disability at a level meaning that they cannot access the measures or intervention.Screening results that indicate a severe mental health disorder not considered suitable for the trial intervention due to the clinical need for immediate intervention, e.g. active suicidality and psychosis.Actively receiving intensive psychological input focused on cognitive and/or behavioural strategies to intervene with emotional or behavioural difficulties at the time of the assessment or due to have such input during active phase of treatment.Refusing to consent to the research team contacting their general practitioner (GP)/other relevant health professionals about their inclusion in the research.Refusing to have the trial therapy sessions audio and/or video recorded.Unable to complete the measures despite all reasonable efforts being made to assist.

### Who will take informed consent? {26a}

The order of screening procedures, consent and pre-randomisation assessments is as follows:
Families may be approached in clinic/hospital by a member of the research team and asked a few brief questions to determine their eligibility for participation and depending on their answers to these questions, they may be asked to complete the SDQ. Families may also be identified by clinicians who are familiar with them. In the latter situation, the clinical team will make contact with the family to ask them if they are interested in being contacted by the MICE trial team or wish to contact the MICE team directly. They will be asked the same questions to establish eligibility.The parent (and child) must give verbal consent to complete the SDQ and agree to being contacted with the results. They will be offered the choice of completing the SDQ in clinic, online or alone in their own time or with support (via the telephone/online or in person).Once the SDQ is completed, a member of the research team will inform the family of the results by telephone, letter, in person or secure email.If the results of the SDQ indicate that the participant may be suitable for the trial, the parent/carer will be given the participant information sheet (PIS) and Informed Consent Form (ICF). The participant will be given an age appropriate PIS according to their developmental age and an ICF or Assent Form.Written informed consent will be obtained from the parent/carer. Written informed consent or assent will be obtained from the participant. Participants aged 16 to 18 years must provide written informed consent if able to do so. If a participant is aged 16 to 18 years and lacks capacity to consent for themselves then their parent/carer should provide written informed consent on the participants’ behalf. Participants aged under 16 years should provide written informed assent if appropriate. The informed consent and assent process may take place by telephone but written informed consent/assent must subsequently be provided to the trial team (either by post, email or at a visit for trial records).

### Additional consent provisions for collection and use of participant data and biological specimens {26b}

The consent form includes consent for future contact regarding ancillary studies, including those related to data linkage with national datasets.

### Explanation for the choice of comparators {6b}

One potential advantage of MATCH-ADTC over existing protocols is that it can be used to treat the significant proportion (approximately 40%) of patients who have multiple mental health problems [18]. Other advantages are that the intervention is designed to be adapted for a diverse range of children, ages and problems and can be delivered in a range of social and healthcare services, including neurological services, by non-mental health specialists. In addition, it can be delivered over the telephone or via virtual online video platforms. The comparison against assessment-enhanced usual care ensures that we can determine the added value over existing service provisions.

### Intervention description {11a}

#### Assessment-enhanced usual care

Usual care for mental health disorders varies by site but typically includes referral to CAMHS or hospital-based paediatric psychology services (see Fig. 1). This intervention is considered as ‘assessment-enhanced’ usual care since those in this arm will have completed the DAWBA and the results of the DAWBA will be provided as information to the GP, referrer and other clinical team members involved as appropriate (e.g. neurologist or paediatrician).

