### Sample size {14}

The sample size is 334 children and young people with epilepsy, and their parents /carers.

Previous effect size (ES; standardised magnitude of the effect) estimates for MATCH-ADTC using measures comparable to the SDQ range from 0.51 to 0.65 [14, 15]. Previous published research has estimated the ES for usual care in UK CAMHS to be 0.16–0.2 [47]. We have therefore conservatively based our calculation on an ES = 0.3 which is modest for a psychological intervention study. Our small pilot study comparing the guided self-help psychological intervention against a waitlist control found a large effect size.

A total sample size of 334 children has been chosen as this could detect an effect size of 0.3 for the SDQ, at the 5% significance level with 80% power, assuming an average of 14 children per therapist, an intraclass correlation coefficient (ICC) of 0.01 for therapist effects, a correlation of 0.5 between baseline and follow-up SDQ, and a loss to follow-up rate of 10%. We will take steps to minimise the amount of missing data. A generalised mixed model will be used to analyse the primary outcome adjusting for baseline SDQ and minimisation variables.

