## Statistical methods

### Statistical methods for primary and secondary outcomes {20a}

Patient characteristics at the time of randomisation will be summarised using mean and SD for continuous variables which are approximately normally distributed, median and interquartile range (IQR) for variables which are not normally distributed, or by frequencies and percentages for categorical variables. All statistical hypothesis tests will use a two-sided *p* value of 0.05 unless otherwise specified. All confidence intervals (CIs) presented will be 95% and two-sided. All statistical analysis will be performed using Stata (StataCorp, College Station, TX, USA) or an alternative package.

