#### Primary outcome

The primary outcome is the difference between the intervention group and the control group in the total difficulties score of the parent-reported SDQ at 6 months post-randomisation.

The total difficulties score of the SDQ has a range of 0–40. Mixed effect linear regression will be used to determine if there is any difference in the total difficulties score due to intervention. The model will include fixed effects for intervention group, baseline SDQ total difficulties score and the stratification factors; age (< 11 versus 11+), primary mental health disorder (anxiety, depression, disruptive behaviour or trauma), presence of autistic spectrum disorder (yes/no) and presence of intellectual disability (yes/no). A random factor, *Therapist*, will be included to take account of therapist effects. Results will be presented as adjusted treatment effect and the associated 95% CI. If the intervention is effective, we would expect to see a reduction in the total difficulties score (higher total difficulties score indicates a higher risk of a diagnosis of mental illness).

The primary analysis will be conducted following the intention-to-treat principle in accordance with the randomised intervention. All efforts will be made to ensure that the primary outcome data is collected for all patients, whether or not they complete their randomised treatment. Missing baseline data are not anticipated since baseline data are completed prior to randomisation and must be recorded to allocate treatment. All patients with reported outcome data will be included in the analysis. The primary analysis is likelihood based and therefore robust to the assumption of missing-at-random, but should substantial missing data be encountered, reasons for missingness will be explored and a sensitivity analysis will be undertaken to investigate the validity of the missing at random assumption.

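### The primary model has no site term although the protocol says usual care differs by site, so the reported confidence interval may be wider than necessary

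*Protocol article*

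**What the plan says.** Under Intervention description {11a}, Assessment-enhanced usual care, the protocol article describes the comparator: "Usual care for mental health disorders varies by site but typically includes referral to CAMHS or hospital-based paediatric psychology services". Children in the MATCH-ADTC arm may also use usual care, so local provision bears on both arms. Study setting {9} describes recruiting clinics as "ranging from highly specialist to general hospitals, and from a range of populations served", and says therapists are NHS staff of several professions employed in epilepsy services.

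The Primary outcome part of Statistical methods {20a} lists the model terms: fixed effects for arm, baseline SDQ total difficulties, age group, primary disorder, autism and intellectual disability. A random therapist factor "will be included to take account of therapist effects". Site does not appear. The secondary models are adjusted for the stratification factors, again without site. Sample size {14} allows for therapist clustering only. No reason is given for leaving site out.

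**The concern.** The protocol names site as a source of variation in care, and its published term list then leaves site out of the model. Individual randomisation puts children of both arms in the same site, so a site's general outcome level largely drops out of the comparison. A model without site cannot see this.

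If each therapist works in one site, and the therapist term applies to MATCH-ADTC children, then a high- or low-scoring site looks like a high- or low-scoring therapist. Its variance is charged to the treatment estimate as clustering. In the control arm the same variance falls into the residual. If therapists serve several sites, nearly all of it falls into the residual. Either way the reported standard error can exceed what the design delivers. What is at stake is the width of the primary interval and some power, not validity.

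**Working it through.** **1. The plan's own figure.** Sample size {14} states: "A total sample size of 334 children has been chosen as this could detect an effect size of 0.3 for the SDQ". Its remaining inputs are a cluster size of 14 per therapist, therapist ICC 0.01, baseline correlation 0.5, 10% loss, power of 80% and a 5% level.

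- Per arm, unadjusted: 2 × (1.960 + 0.842)² / 0.3² = 174.4, so 175
- Baseline adjustment: 175 × (1 − 0.5²) = 131.25, so 132
- Design effect 1 + 13 × 0.01 = 1.13: 132 × 1.13 = 149.2, so 150
- Loss: 150 / 0.9 = 166.7, so 167 per arm, 334 in total

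The figure reproduces. With 150.3 analysed per arm, SE = √(2 × 0.75 × 1.13 / 150.3) = 0.106. Power is Φ(0.3/0.106 − 1.96), about 80.6%, with no allowance for site.

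**2. Assumptions for the site question.** 300 analysed; adjusted variance 0.75; therapist ICC 0.01, in the MATCH-ADTC arm only; 12 equal sites with one therapist each. The 12 comes from 167/14, which counts therapists; the article gives no number of sites. The site share ρ of the adjusted variance is varied because the documents give none.

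**3. Standard errors by generalised least squares, variances taken as known.** Let S mark pairs of children in the same site and T pairs of MATCH-ADTC children with the same therapist.

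- True covariance: 0.75 × [ρS + 0.01T + (1 − ρ − 0.01)I]
- As read without a site term: 0.75 × [(ρ + 0.01)T + (1 − ρ − 0.01 + ρ/2)I]. The MATCH-ADTC share goes to therapist; the control share is spread over the pooled residual.

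Hand check at ρ = 0.05, with an exactly even split in every site:

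- Without site: √(0.045/12 + 2 × 0.72375/150) = √0.0134 = 0.116
- With site: √(0.0075/12 + 2 × 0.705/150) = √0.010025 = 0.100

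Averaged over random allocations, which are not exactly even within sites:

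| ρ | Reported SE, no site | True SE of that estimate | SE with random site | Interval too wide by | Analytic power, without / with |
|---|---|---|---|---|---|
| 0 | 0.1027 | 0.1027 | 0.1027 | 0% | 83.2% / 83.2% |
| 0.01 | 0.1055 | 0.1026 | 0.1025 | 2.9% | 81.1% / 83.3% |
| 0.02 | 0.1083 | 0.1024 | 0.1023 | 5.9% | 79.1% / 83.5% |
| 0.05 | 0.1161 | 0.1019 | 0.1012 | 14.7% | 73.3% / 84.2% |

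Power at ρ = 0 exceeds 80.6% because therapist clustering is placed in one arm here, whereas the plan inflates both.

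The third and fourth columns nearly agree. The estimate itself loses almost nothing; it is the reported SE that is too large.

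**4. Therapists not nested in sites.** The interval is 0.1%, 0.4%, 1.3% and 3.7% wider at ρ = 0.01, 0.02, 0.05 and 0.10 with 12 sites. With 6 sites the figures are 0.2%, 0.6%, 1.9% and 4.4%.

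**5. Simulation with estimated variances.** REML, 1,000 runs per setting, nested therapists, site as *fixed* effects; power without / with site:

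| ρ | 12 sites, 1 therapist each | 6 sites, 2 therapists each |
|---|---|---|
| 0 | 81.0% / 76.0% | 84.0% / 82.8% |
| 0.01 | 81.1% / 79.8% | 82.5% / 82.7% |
| 0.02 | 80.5% / 81.3% | 81.1% / 81.6% |
| 0.05 | 75.8% / 79.7% | 76.2% / 82.3% |

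Mean estimates for ρ from 0.01 to 0.10 lay between 0.295 and 0.303 for a true 0.3, so there is no bias. Fixed site effects cost power when site variance is nil or very small.

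A smaller check used a *random* site intercept (12 unequal sites, 200 runs per setting). At ρ = 0 power was 80.5% with the term and 78.5% without; at ρ = 0.01 the SE was 0.106 with it and 0.109 without. The Monte Carlo error of each power figure is about √(0.8 × 0.2/200), or 2.8 points, so this shows only that no loss was visible. The random intercept was not simulated at ρ = 0.05.

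**The case against.** The strongest reply is that nothing here is stated wrongly. The sample size reproduces, the estimate is unbiased, and an overlong interval errs on the safe side. All of that stands.

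The size of the effect also depends on things the documents do not say. Study setting {9} places therapists in epilepsy services but does not tie each to one site. The therapist's initial face-to-face assessment makes local therapists plausible, but delivery mainly by telephone or video would allow work across sites. The article does not say that the therapist term applies to one arm only. Baseline SDQ and the stratification factors may already absorb part of the case-mix between sites. These points stand too, and they limit the size of the claim without removing it.

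A reader might infer that power falls to 73%, or to 65% at a site share of 0.10 (64.9% without site against 85.8% with it, analytically). Those figures need a site share of 0.05 or more, one therapist per site, a therapist term in one arm and known variances, all together. The documents support none of these directly.

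A reader might also infer that site should have been a minimisation factor. Sequence generation {16a} gives reasons for its four factors. A further factor with many small levels competes with balance on those, and in an open-label trial balancing by site can make allocation easier to predict. Uneven splits within small sites are ordinary chance and show no bias.

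**Conclusion.** The point holds as a modest loss of efficiency in the stated primary model. Under nesting with 12 sites and known variances, the reported interval is about 3%, 6% or 15% too wide at site shares of 0.01, 0.02 and 0.05. Simulated power gains are smaller: about 4 points at 0.05 with 12 sites, about 6 with six sites, and close to nothing at 0.01 to 0.02, where the current model already gives roughly the planned 80%. Without nesting the excess width is 0.1% to 4.4% for site shares from 0.01 to 0.10.

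Site share, number of sites and nesting are all assumptions. There is no bias, no added false-positive risk and no error in 334. The case for acting is that the protocol itself says sites differ and the change costs almost nothing.

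**What to change.** Add a random intercept for site, common to both arms, to the primary model and to the secondary mixed models, alongside the therapist term. Make the change before the analysis. Use a random rather than a fixed effect, since fixed effects lost power in the simulation when site variance was nil or very small. Even with one therapist per site the two terms can be separated, because control children in that site inform the site term but not the therapist term.

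The cost is one variance parameter on a variable known for every child. With many small sites its variance may be estimated at or near zero, in which case the model reduces to the current one.

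A common intercept does not model a treatment effect that itself differs by site, and should not be described as doing so. The minimisation factors and the sample size need no change.
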